## 327 Checking the inclusion and exclusion criteria

328 The examination of the inclusion and exclusion criteria of potential study patients  
329 ("screening") is performed using a predefined checklist. All patients who meet the inclusion  
330 criteria are documented in a central "Screening Log" (**Appendix 2**) at the study center. This  
331 log will also indicate whether the patient was included in the study or for what reason, if any,  
332 the patient was not included. If a patient fulfills all inclusion criteria and there are no exclusion  
333 criteria, he/she is to be entered in the patient identification list with the date of study  
334 inclusion.

## 335 7.2 Patient education and consent

336 Each patient is informed about the nature, significance, objectives, possible risks, expected  
337 benefits, implications and other aspects of the study by means of a discussion between the  
338 study physician and the patient. The patient receives the written patient information (**see**  
339 **Appendix 3**). The study physician makes sure that the patient has understood the  
340 information. After the information session, each patient is given sufficient time and  
341 opportunity to clarify any unanswered questions and to decide on his or her participation.

342 Each patient signs and dates his or her consent to participate in the study in writing on the  
343 consent form. The patient's consent must also explicitly refer to the collection and processing  
344 of personal data. Therefore, patients are explicitly informed about the purpose and scope of  
345 the collection and the use of these data, especially health data.

346 If a patient is unable to sign the consent personally, a witness must be present during the  
347 informed consent process who can confirm that the patient has given verbal information and  
348 consent by signing.

349 Since no invasive procedures are performed as part of the study and the study-related  
350 intervention is merely counseling and documentation, with the decision to implement the  
351 recommendation remaining at the discretion of the treating physician, consent may be  
352 obtained from the health care proxy or a court-appointed guardian in the case of a patient  
353 who lacks capacity to consent.

354 One copy of the signed consent form (copy or 2nd original) is given to the patient or  
355 caregiver. The other remains at the study center. The SUPPORT study center receives a  
356 copy by fax message.

357 The patient or caregiver may withdraw consent to study participation at any time and without  
358 giving reasons. It is requested to state the reason for withdrawal, but it is pointed out that this  
359 is a voluntary statement. The time of withdrawal of consent to treatment or study is to be  
360 documented in the patient's file by the study team at the center.

361 The presence of pregnancy is not an exclusion criterion.

362 If it is subsequently determined that there was a violation of the inclusion and exclusion  
363 criteria, the study management decides whether the patient should be included in the  
364 statistical evaluation of the "per protocol analysis". The documentation of the patient is  
365 independent of this. All included patients are to be included in the ITT analysis.

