## 7.11 End of the study

### 7.11.1 Regular end of study

The regular end of the study is defined as the date on which the last patient has completed the follow-up ("Last Patient Out - LPO").

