### 9.2 Definition of evaluation collectives

The primary analysis will be performed according to the intention-to-treat (ITT) principle - i.e. in all included patients. Sensitivity analyses will be performed in the per-protocol (PP) collective, for which rules will be defined prior to study completion.

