## 9.5 Statistical analysis

Differences in the primary end point, 30-day all-cause mortality, are determined confirmatorily within the framework of a generalized linear mixed model (GLMM). This was specified in more detail by Reich et al (25) and also forms the basis of the case number calculation. This model is suitable to represent the dependence structure by the clusters and the period effects for a dichotomous outcome variable, where the null hypothesis of no treatment effect can be rejected if the two-sided p-value of the Wald test statistic for the fixed effect *group* can be rejected at the two-sided significance level  $\alpha=5\%$ . The confirmatory test is performed according to the ITT principle, with missing endpoint data in included patients replaced by multiple imputation. Further sensitivity analyses of the primary endpoint are "worst case" imputations as well as analyses in the PP collective. In addition, the *a priori* defined subgroups center, gender and age groups (quartiles) of the patients will be analyzed stratified. For these analyses as well as for the adequate statistical analyses of the secondary endpoints, which will also be performed within GLMM, no multiplicity adjustment is planned.

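### Section 7.2 lets study management decide case by case which eligibility violators enter the per-protocol analysis, with no stated blinding and no link to the rules promised in Section 9.2

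*Protocol*

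**What the plan says.** Section 7.2 covers violations that come to light after inclusion: "If it is subsequently determined that there was a violation of the inclusion and exclusion" "criteria, the study management decides whether the patient should be included in the" PP evaluation. The clause names who decides. It gives no criterion, no latest date, and nothing on what the decision-maker may know. The same paragraph protects the main analysis set: "independent of this. All included patients are to be included in the ITT analysis".

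Section 9.2 makes ITT the primary analysis and assigns the PP collective to sensitivity analyses, "for which rules will be defined prior to study completion". Section 7.11.1 fixes that end point: "The regular end of the study is defined as the date on which the last patient has completed the follow-up".

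Section 9.5 runs the confirmatory test on the ITT set. As further sensitivity analyses of the primary endpoint it lists worst-case imputation and "analyses in the PP collective".

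Only patients are blinded (Synopsis; Section 4.2). Under Section 7.1 the study center carries out the consult for intervention-arm patients and makes the follow-up calls at 30 and 90 days.

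**The concern.** A PP analysis checks a primary result only if membership is settled without regard to how patients fared. Here the protocol states a procedure that does not ensure this: a decision per patient, taken whenever a violation is found, with no masking. Some exclusion criteria in Section 6.2 call for judgement, above all a life expectancy below 90 days. Such a judgement, made in retrospect, can be coloured by knowing whether the patient died.

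At stake is the credibility of one of the two kinds of sensitivity analysis that Section 9.5 names for the primary endpoint. If the ITT result is close to the threshold, readers will look to the PP result for support. A set chosen with outcomes in view cannot give it.

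**Working it through.** **Timing.** Follow-up runs 90 days from diagnosis (Section 7.9) and the primary endpoint is read at day 30. The study ends when the last patient finishes follow-up (Section 7.11.1). The last patient therefore passes day 30 about 90 − 30 = 60 days before study end. PP rules written in those 60 days would satisfy Section 9.2, yet every patient would have passed day 30 and nearly all outcomes would be on record. This is the latest date allowed, not necessarily the date that will be used.

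**Are the two sections linked?** Section 9.2 speaks of rules. Section 7.2 speaks of a decision and does not refer to Section 9.2. Nothing says that the decision must follow the rules.

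**Is the decision masked?** Arm and death are both available at the study center (Section 7.1). The randomization list stays inaccessible (Section 7.3), but the consult itself reveals the current arm. No visible provision masks study management.

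**Size, by illustration.** The protocol gives no figure to reproduce here, so the death counts are assumed. The inputs are:

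- 225 patients per arm, half of the 450 to be analysed (Synopsis).
- Control mortality of about 25%, the hospital mortality in Section 1.3, and of 50% and 60%, from the control range of 0.5 to 0.7 in Section 9.3.
- A pooled two-proportion z-test, ignoring clustering and period: p̄ = (x₁ + x₂)/(n₁ + n₂) and z = (x₂/n₂ − x₁/n₁) / √[p̄(1 − p̄)(1/n₁ + 1/n₂)].

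Example with 56 control deaths:

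- Nobody left out: 41/225 = 0.1822 against 56/225 = 0.2489. p̄ = 97/450 = 0.2156, SE = 0.0388, z = 0.0667/0.0388 = 1.72, p = 0.086.
- Three intervention deaths left out: 38/222 = 0.1712 against 0.2489. p̄ = 94/447 = 0.2103, SE = 0.0386, z = 0.0777/0.0386 = 2.02, p = 0.044.
- Three control deaths left out instead: 0.1822 against 53/222 = 0.2387. SE = 0.0386, z = 0.0565/0.0386 = 1.47, p = 0.14.

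Three patients are 3/450 = 0.7% of the analysed total. The table gives the number of intervention deaths that must be left out to bring p below 0.05.

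| Control deaths of 225 | Intervention deaths of 225 | p, nobody left out | Left out | p after |
|---|---|---|---|---|
| 56 | 41 | 0.086 | 3 | 0.044 |
| 56 | 44 | 0.174 | 7 | 0.041 |
| 56 | 46 | 0.260 | 9 | 0.046 |
| 112 | 94 | 0.089 | 5 | 0.048 |
| 112 | 101 | 0.299 | 17 | 0.0498 |
| 135 | 117 | 0.087 | 6 | 0.048 |
| 135 | 124 | 0.294 | 21 | 0.048 |

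With 250 per arm the counts again run from 3 to 21. Starting from p just under 0.09, three to six one-sided exclusions are enough. Starting from p of about 0.26 to 0.30, it takes 9 to 21.

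**The case against.** The case for leaving the text alone has real substance.

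- **Rules are promised.** Detailed PP criteria commonly sit in a SAP, which is not shown. Section 7.2 can be read as naming the decision-maker and Section 9.2 as supplying the rules. No interim evaluation is planned (Sections 4.6 and 9.4), so the plan provides for no tabulation by arm before the end. This stands in part: an absent PP definition is not the complaint. But Section 7.2 still grants a discretion that no rule is said to bind, and individual deaths are known without any tabulation.
- **Eligibility is documented early.** Section 7.1 provides for a predefined checklist and a screening log, and Section 10.3.2.1 puts the criteria in the CRF. This should keep late-found violations few. The protocol gives no expected number.
- **The illustration is extreme.** It starts near the threshold, removes only deaths from only one arm, and uses a simpler test than the planned mixed model. That is correct. It shows sensitivity, not a forecast.

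Stronger readings are tempting and should be resisted. A reader might infer that study management knows each patient's arm and outcome when it decides. The protocol shows only that the study center has both. The visible text does not define the membership of study management, and the pages on persons and bodies are not available. A reader might also infer that violations will be found mainly in patients who died. That is plausible, but nothing in the protocol documents it.

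**Conclusion.** The point holds as a weakness in a stated procedure. Section 7.2 leaves PP membership of eligibility violators to an unmasked decision for each case, and Section 9.2 neither binds that decision nor requires rules before outcomes are known. It does not put the trial's main conclusion in doubt, since the confirmatory test keeps all included patients (Sections 7.2, 9.2 and 9.5).

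The effect is limited to the PP sensitivity analysis and matters mainly near the threshold, where a few selective exclusions could change its result in either direction. That size rests on assumed death counts, on exclusions confined to deaths in one arm, and on independent patients. The actual number of late-found violations is unknown. This is a desirable correction rather than an essential one.

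**What to change.** Amend Sections 7.2 and 9.2 together so that they state one procedure:

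1. Replace the discretion in Section 7.2 with written PP criteria, and have Section 9.2 refer to the same criteria. Fix them before database closure and before any outcome is tabulated by arm.
2. Exclude a patient for an eligibility violation only on information dated before inclusion.
3. Have the criteria applied to a listing stripped of arm and outcome, by someone not involved in the consults or the follow-up calls. The visible protocol does not show the biometrician to be masked, so that role should not be assumed to qualify.
4. Do not let a missed consult alone exclude a patient who died before it could be given. Such a rule would remove early deaths from the intervention arm only and add a bias of its own.

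The cost is a few sentences in two sections, one masked listing, and the loss of case-by-case discretion. Sample size, follow-up and the confirmatory analysis do not change.

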## 366 7.3 Randomization

367 Randomization of the hospitals to the sequence A-B or B-A will be performed before the start  
368 of the study as block randomization with variable block length. It is performed with the help of  
369 randomization software at Jena University Hospital by a study-independent person of the

370 Center for Clinical Studies (ZKS) Jena. The randomization list will be kept inaccessible until  
371 the end of the study.

## 372 7.4 Treatment phase

373 A treatment phase in the actual sense does not exist in the SUPPORT study. The patients in  
374 the intervention group should be treated according to the infectious diseases consil. The  
375 implementation of the consil is the responsibility of the treating physicians of the study  
376 centers. Treatment measures carried out are to be documented in the patient file in such a  
377 way that the data can be recorded by the SUPPORT study nurse during the on-site visits to  
378 the study centers.

## 379 7.5 Description of laboratory and other investigations and methods

380 All medications (beta-lactam antibiotics, vancomycin, etc.) or examinations (e.g.,  
381 transesophageal echocardiography) recommended in the infectious disease consult are  
382 routinely used in clinical practice.

## 383 7.6 Examinations within the framework of discharge

384 No special examinations are scheduled as part of the discharge process.

## 385 7.7 Follow-up surveys

386 The survival of the patients and the recurrence rate will be recorded up to 90 days after  
387 diagnosis of SAB. For this purpose, the patients or, if they are not available, the primary care  
388 physician or the study centers will be interviewed by telephone 30 and 90 days after  
389 diagnosis. Patient visits are not planned.

## 390 7.8 Description of the individual visits

391 No patient visits will be conducted as part of the study.

## 392 7.9 End of study participation

393 The regular study end date for each study participant is 90 days after diagnosis of SAB.

## 394 7.10 Premature withdrawal of a patient from the study (discontinuation 395 criteria).

396 Each participant has the right to withdraw from the study prematurely at any time at his own  
397 request and without giving reasons (consent is withdrawn), without any disadvantages for his  
398 further (medical) treatment.

399 If a patient withdraws consent or wishes to discontinue treatment, this must be documented  
400 accordingly as a reason for discontinuation, stating the time, in the patient record and in the  
401 CRF.

402 If a patient cannot be contacted at the 30-day follow-up, this does not automatically mean  
403 that the study has been discontinued. The 90-day follow-up will still be performed.

## 7.11 End of the study

### 7.11.1 Regular end of study

The regular end of the study is defined as the date on which the last patient has completed the follow-up ("Last Patient Out - LPO").

### 7.11.2 Premature end of study/discontinuation of the entire study

Reasons for premature termination of the entire study may include:

- Decision of the study management in case of unacceptable risks under benefit-risk consideration
- new scientific findings during the term of the study
- non-adequate recruitment rate
- No study inclusion within the first 3 months after the start of recruitment.

The study director informs the lead ethics committee of the reasons for a planned discontinuation of the entire study. This committee decides after detailed consultation; if it approves the application, the study director is obliged to inform the participating study centers immediately.

## 8 Adverse events/complications

### 8.1 Adverse events

SUPPORT is not a study in the sense of the AMG. All recommended measures and medications are routinely used in everyday clinical practice. Specific adverse events due to the intervention (telephone consultation) are not expected, since the telephone consultation only suggests treatment options that the treating physician can implement. Complications of the recommended and implemented diagnostic and therapeutic measures (e.g. esophageal perforation after transesophageal echocardiography, contrast medium- or vancomycin-induced renal insufficiency, pneumothorax when changing a CVC, etc.) are documented. ) are documented.

### 8.2 Possible complications and/or risks

Complications are defined as all events that are or could be related to the therapeutic and diagnostic measures recommended in the infectious disease consultation. These include complications that may occur as a result of the medications (intolerances to the recommended antibiotic or contrast agent when performing contrast computed tomography) or as a result of medically interventional complications, such as those that may occur during abscess cleavage or transesophageal echocardiography. The drugs to be recommended are approved for the treatment of *S. aureus* bacteremia by the "European Medicines Agency" (EMA). The medical measures to be recommended belong to routine clinical examinations, about the risks of which the treating physician is obliged to inform the patient before the examination. Therefore, for the SUPPORT study, there are no specific risks for the participating patients that exceed the clinical routine.

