| Target population/disease             | Patients with Staphylococcus aureus bacteremia.                                                                                                                                                                                                                                                                                                                                                                                                                                                                                                                                                                                                                                                |
| Study design/methodology              | Prospective randomized, single-blind, controlled two-arm (intervention vs. control) multicenter trial with cross-over design. The intervention is the provision of a non-requested infectious disease telephone consult. The control group will not receive a telephone consult. The study duration in one group before cross-over is to be 12 months.
Randomization: 1:1 cross-over
Blinding: simple, i.e., patients are not told which group (intervention or control) they are in; blinding of treating physicians/study centers is not possible.
Intervention group: non-requested telephone consult.
Control group: no telephone consultation, follow-up only.
Follow-up: 90 days |
| Aims of the clinical trial/objectives | Primary Objective:
To demonstrate efficacy (30-day all-cause mortality) and safety of nonrequested infectious disease consults compared with standard care without telephone consults in patients with SAB.                                                                                                                                                                                                                                                                                                                                                                                                                                                                                 |

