## 3 Study objectives

### 3.1 Primary study objective and primary endpoint

The primary study objective of the SUPPORT study is to determine whether 30-day all-cause mortality can be reduced in patients with SAB using telephone consults with a clinical infectious disease specialist in Thuringia (compared to no such telephone consults). This is a superiority study.

**Primary endpoint:** 30-day all-cause mortality

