## 7 Course of studies

### 7.1 Detailed study process

Information about a microbiological blood culture result *positive* for *S. aureus* is automatically reported to the SUPPORT team via the AlertsNet infrastructure (Electronic Blood Culture Registry, EBCR). However, data management is done separately. The system sends a fax to the treating hospital with the patient's clinical name, -year of birth, *subject identification code* (SIC) and microbiological findings. The study center at the UKJ, which is informed at the same time, does not receive any clear name information but only the information of a SAB detection in a specific institution and the automatically generated case code (SIC). The study center contacts the study physician at the clinical institution and, based on the relevant positive microbiological findings and using the SIC, asks for the patient to be included in the study. If the patient agrees to participate in the study after being informed by the study physician, the signed consent form is faxed to the study center. Only with this fax does the study center thus receive clear name information on the SAB-positive patient. Thereupon, for patients of the intervention arm, the telephone consultation with the treating physician is performed and subsequently the consultation is confirmed by fax (incl. therapy proposal). For patients in the control group (no infectious disease consultation), the two aforementioned steps are omitted. After inclusion in the study, only the informed consent form is faxed to the study center. A consultation is not performed for these patients.

The SUPPORT study nurse documents the data of the study patients pseudonymously in the CRF as soon as possible during her on-site visits. After 30 and after 90 days, a follow-up call is made to the patients by the study center. The contact details for this are recorded separately in the consent form (**Figure** and **Section 14.2**).

[figure not shown]

\*EBCR: Electronic Blood Culture Registry

325

326 **Figure:** Flow chart for the SUPPORT study.

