### 8.3 Recording and documentation of complications

Complications are recorded over a period of 90 days after inclusion in the study. In case of doubt, the study outpatient clinic should be contacted by telephone. In case of death, the

cause of death should be documented. Unexpected, previously unknown complications for which a causal relationship with the recommended measures cannot be ruled out will be reported to the study participants within one week.

All complications will be documented in the patient's chart and later recorded in the CRF by the SUPPORT study nurse.

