#### 10.3.2.5 Infection focus

- Intrathoracic infection
- Urogenital/renal infections
- Infection of the central nervous system
- Bone and joint infections
- Infections of the cardiovascular system

- 566 -HNO/oropharyngeal infections
- 567 -Intraabdominal infections
- 568 -Skin and soft tissue infections
- 569 -Postoperative wound infections
- 570 -Flexure tube as suspected source of infection
  
- 571 10.3.2.6 Characteristics of blood culture
- 572 -Date of blood culture collection
- 573 -Location of blood culture collection
- 574 -Presence of foreign bodies or prostheses
- 575 -Further positive blood cultures
- 576 -Detection of other bacteria
  
- 577 10.3.2.7 Presence of SIRS criteria
  
- 578 10.3.2.8 Organ dysfunction within 7 days of 1st positive blood culture.
- 579 -Acute encephalopathy
- 580 -Thrombocytopenia
- 581 -Arterial hypoxemia
- 582 -Renal dysfunction
- 583 -Metabolic acidosis
  
- 584 10.3.2.9 Septic shock within 7 days after 1. positive blood culture.
  
- 585 10.3.2.10 Severity of SAB
- 586 -uncomplicated
- 587 -complicated
  
- 588 10.3.2.11 PITT score on the day of blood culture collection (24).
  
- 589 10.3.2.12 Charlson comorbidity index (23)
  
- 590 10.3.2.13 Recommended measures/implementation of the recommended measures
- 591 -Time
- 592 -Follow-up blood cultures
- 593 -Focus remediation
- 594 -Transesophageal echocardiography
- 595 -other proposed measures
  
- 596 10.3.2.14 Laboratory values on the day of the positive blood culture
- 597 - Creatinine
- 598 -Creatinine Clearance
- 599 -Bilirubin
- 600 -Lactate
- 601 -CRP
- 602 -PCT
- 603 -ALAT
- 604 -ASAT
- 605 -AP
- 606 -leukocytes
- 607 -platelets
- 608 -neutrophil granulocytes
- 609 -Ferritin

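### The protocol ties the definition of a complication to the consultation, which control patients do not get, while its CRF list applies to both groups and its synopsis promises a safety comparison

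*Protocol*

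**What the plan says.** **Definition.** Protocol 8.2 reads: "Complications are defined as all events that are or could be related to the therapeutic and diagnostic measures recommended in the infectious disease consultation". Section 8.1 likewise provides for documentation of "Complications of the recommended and implemented diagnostic and therapeutic measures". The one-week reporting rule in 8.3 also refers to the recommended measures.

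**Control group.** Section 7.1 says of control patients: "A consultation is not performed for these patients".

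**Recording.** Section 8.3 says: "Complications are recorded over a period of 90 days after inclusion in the study". It sends all complications to the CRF and does not restrict this by group. CRF section 10.3.2.16 lists events by drug or procedure (for example renal failure on vancomycin, or oesophageal rupture during transesophageal echocardiography), plus antibiotic allergy, *C. difficile* enteritis and an open category. None of these items requires that a consultant recommended the measure. CRF section 10.3.2.13, which covers follow-up blood cultures, focus control and transesophageal echocardiography, is headed "Recommended measures/implementation of the recommended measures".

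**Objective.** The synopsis (1.4) gives the primary objective as: "To demonstrate efficacy (30-day all-cause mortality) and safety of nonrequested infectious disease consults compared with standard care without telephone consults". Section 3.1 gives it as to "determine whether 30-day all-cause mortality can be reduced in patients with SAB using telephone consults" and does not mention safety. Sections 3.2 and 9.1 list no complication endpoint.

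**The concern.** A safety comparison needs the same event definition in both groups. Here the definition depends on having received the intervention. Sections 7.5 and 8.1 describe the drugs and examinations as routine care, so control patients will receive many of them and can suffer the same harms. Under 8.2 as worded, renal failure on vancomycin is a complication if the consultant recommended vancomycin, and is not one if the treating physician chose it unaided.

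What is at stake is ascertainment. The study nurse abstracts complications from the chart, and the CRF carries the group allocation (10.3.2.1). Only patients are blinded, and 11.3 plans no independent monitoring. If the nurse applies 8.2, control events may be left out. If she works down the list in 10.3.2.16, they will not be. Nothing in the protocol says which rule prevails. Any resulting error runs in one direction, towards apparent harm from the consultation, and it is hard to undo once abstraction is complete.

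**Working it through.** The protocol states no complication rate, safety margin or safety sample size, so there is no planned figure to reproduce. The check is a comparison of sections, followed by an illustration.

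**1. Sections side by side**

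| Protocol section | Tied to a recommendation? | Applies to control patients as worded? |
|---|---|---|
| 8.1, documentation of complications | Yes | No |
| 8.2, definition | Yes | No |
| 8.3, 90-day recording and transfer to CRF | No | Yes |
| 8.3, one-week reporting | Yes | No |
| CRF 10.3.2.13, measures | Yes, by its heading | Unclear |
| CRF 10.3.2.16, complication list | No | Yes |
| Synopsis, primary objective | Safety compared with standard care | Requires control data |
| 3.1, 3.2, 9.1 | Safety or complications not listed | Not applicable |

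The recording instructions cover both groups. The term they use, complications, is the one that 8.2 defines through the consultation.

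**2. Effect of partial under-recording**

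Assume equal true rates in both groups, full recording in the intervention phase, and a fraction f of control events recorded. The apparent risk ratio is then 1/f:
- f = 1 (CRF list followed in both groups): ratio 1, no bias.
- f = 0.5: ratio 1/0.5 = 2.
- f = 0 (8.2 applied literally): control count zero, ratio undefined.

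The protocol does not determine f.

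**3. The literal extreme, for scale only**

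Inputs: 15 centres with 15 patients per phase (9.3), so 15 × 15 = 225 per condition and 450 in total. Clustering is ignored. The complication rates are assumptions.

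For x events against 0 with 225 patients on each side, the two-sided Fisher p-value is 2 × C(225, x) / C(450, x):
- x = 5: p = 0.061
- x = 6: p = 0.030

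Six counted intervention events are therefore enough for nominal significance. With the same true rate r in both groups, every intervention event counted and every control event dropped, the probability of at least 6 counted events is P(X ≥ 6) with X ~ Binomial(225, r):

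| Assumed true rate r | Expected intervention events (225 × r) | P(X ≥ 6) |
|---|---|---|
| 1% | 2.25 | 0.027 |
| 2% | 4.5 | 0.296 |
| 5% | 11.25 | 0.971 |
| 10% | 22.5 | over 0.99 |

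These are upper limits. Under the literal rule, an intervention-phase event that follows a measure the consultant did not recommend would not count either.

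**4. Recording window**

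Section 8.3 gives 90 days from inclusion, whereas the endpoints in 9.1 run from SAB diagnosis. Complications appear on the CRF under discharge status (10.3.2.15) and as their own section (10.3.2.16, no time limit stated). The 30- and 90-day forms (10.3.2.17 and 10.3.2.18) collect readmission, death and new complaints, but have no complication item. The window needs one explicit statement.

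**The case against.** The strongest reply is that the protocol's data collection is already even-handed. The list in 10.3.2.16 names drugs and procedures without reference to a consultation, 8.3 records all complications, and the nurse abstracts charts in both groups. Section 8.2 also speaks of drugs and measures that are to be recommended, and section 5 describes the consultation as recommending an evidence-based set of interventions. The definition can therefore be read as covering a class of measures, whoever ordered them. No complication comparison is listed in 9.1 or 9.5, so no biased test is prespecified.

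Much of this stands. A reader might infer from 8.2 that control patients cannot have a complication, that complications are the only safety information, or that the safety question cannot be answered. The documents do not support those readings. The CRF allows control events to be recorded. Mortality, recurrence, progression to sepsis or septic shock, septic metastases, readmission and new complaints are collected in both groups. A comparison of some events against zero would arise only if 8.2 were applied strictly against 8.3 and 10.3.2.16. The 10.3.2.13 heading does not show that control data on these measures are omitted, and the benefit-risk stopping reason in 7.11.2 is not linked to any comparison of complications between groups.

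The reply does not remove the ambiguity. The class reading is possible but not stated, 8.1 and 8.2 are worded the same way, and nothing says that the CRF list overrides them. Details of a safety analysis may sit in a statistical analysis plan that is not shown, and their absence is not counted here. Such a plan could not restore control events that were never recorded.

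**Conclusion.** The point holds as an internal inconsistency with a real risk of differential ascertainment. The complication definition in 8.1 and 8.2 depends on the intervention. It conflicts with the recording rule in 8.3 and the list in 10.3.2.16, and it does not fit the synopsis objective of safety compared with standard care. The protocol also disagrees with itself on whether safety belongs to the primary objective.

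The likely direction of bias is against the consultation. Its size cannot be estimated: it ranges from none, if the CRF list is followed in both groups, to the literal extreme shown above. That extreme rests on assumed rates, independent patients and complete omission of control events. The primary endpoint, its test and the sample size are not affected.

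**What to change.** 1. In 8.1 and 8.2, define complications as events that are or could be related to the diagnosis or treatment of SAB, using the 10.3.2.16 list, whether or not a consultation recommended the measure.
2. In 8.3, state that complications are recorded identically and over the same window in both groups, and give one starting point for that window. Add a complication item to the follow-up forms if the 90 days are to be covered.
3. Relabel CRF 10.3.2.13 as measures performed, with a separate yes/no item for whether the measure was recommended. Attribution to the consultation then remains available as a descriptive variable.
4. Reconcile the synopsis with 3.1 and 9.1: either name the between-group complication rate as a secondary safety endpoint, or remove safety from the primary objective. Either choice resolves the contradiction.

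The cost is a change of protocol and CRF wording and a short instruction to the study nurse, who already abstracts these records in both groups. No extra patients or visits are needed. If abstraction has begun, control charts already completed should be checked again against the list.
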